### Study setting

Eligible patients are recruited in the Netherlands, UK and Australia. Approximately 24 hospitals will participate, consisting of both academic and large teaching hospitals. Inclusion of a pilot centre in the Netherlands started in June 2020 and overall recruitment in the Netherlands started in January 2021. Recruitment in the UK and Australia is planned to start in the second quarter of 2021. A list of current study sites can be obtained via the website [30].

### Interventions

After recruitment and consent, an ultrasound scan for fetal biometry, amniotic fluid volume, uterine artery pulsatility index and CPR is performed. The pulsatility indices of both the umbilical artery and middle cerebral artery will be reported aside from the calculated CPR. Depending on the cluster, clinicians will be either blinded or unblinded to the CPR. Expedited delivery is pursued in women with an abnormal CPR – defined as an CPR < 1.1 - in the open arm. In this case we aim to start delivery within 16 h or an elective caesarean section will be advanced. There are no criteria for discontinuing the intervention other than participant request. In this case she will be followed-up for intention-to-treat analysis. Women in the concealed arm will not have their CPR results revealed and will receive routine clinical care (Fig. 1).

**Fig. 1 Fig1:**
[figure not shown]
Flow chart of the CEPRA study design and interventions. ^a^ Blood sample will not be drawn from participants with a normal CPR in the open arm. ASQ: Ages and Stages Questionnaire, CBCL: Child Behaviour Checklist, CPR: cerebroplacental ratio, CTG: cardiotocograph, EQ-5D-5L: European Quality of life 5-Dimension 5-Level, PCL-5: posttraumatic stress disorder checklist for DSM-5, SGA: small for gestational age, WDEQ: Wijma Delivery Expectancy/Experience Questionnaire

A maternal blood sample will be taken from *all participants* in the *concealed arm* and from participants with an *abnormal CPR* in the *open arm* for serum biomarker analyses and will be stored locally. Analyses are performed in batch after study closure.

### Additional studies

Depending on local guidelines and feasibility, the placenta is submitted to the local pathology department for routine examination conform the sampling procedures laid out in the Amsterdam Placental Workshop Group Consensus Statement [31]. We aim to analyse the results of routine placental histology performed within routine clinical care for suspected placental insufficiency. Tissue blocks are stored locally and will be analysed centrally for immunohistochemistry and methylation studies after study closure.

### Follow-up

Follow-up consists of online questionnaires at 6 weeks-, 12 months- and 24 months postpartum (Fig. 1).

### Insurance

According to national legal requirements an insurance is taken out that covers injuries caused by participation of this study. The insurance applies to injuries that become apparent during the study period or within 4 years after trial closure. Also a liability insurance in compliance with national legal requirements is taken out.

## Statistical analysis

### Data analysis plan

The primary analysis will estimate the relative risk (RR) with 95% confidence intervals and *p*-values for the composite perinatal outcomes, using a generalized linear mixed model with log link and binomial distribution, with random intercepts and random slopes per cluster. The primary analysis will be performed according to the intention-to-treat principle. A per protocol analyses will be done as secondary analysis.

Dichotomous secondary outcomes will be analysed using the same method as the primary outcome. Continuous data of secondary outcomes will be assessed using a linear mixed model to estimate mean differences, with random intercepts and slopes as appropriate. Median differences will be calculated as appropriate. A significance level of 5% will be used for all tests. Interim testing for efficacy will not be performed, hence the significance level does not need to be lowered.

Given that all required data is collected for routine patient care in both primary and secondary care, missing data is expected to be limited. Multiple imputation will be used if required.

Data of quality of life measures will be obtained at four time points and will be analysed using generalised estimating equations.

For subgroup analyses we will assess the relationship between pregnancy characteristics, outcomes and abnormal serum biomarkers of PlGF and sFlt-1.

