### Study design

We will conduct an international cluster randomised controlled clinical trial with randomisation at hospital level to either an open (CPR revealed) or concealed arm, performed in the Netherlands, UK and Australia. The protocol was drafted in accordance with the SPIRIT (Standard Protocol Items: Recommendations for Interventional Trials) statements [22]. The trial was registered at the Dutch Trial Registry (NTR 7557) prior to the start of inclusion, and is embedded within the Dutch Society of Obstetrics and Gynaecology’s (Nederlandse Vereniging van Obstetrie en Gynaecologie) NVOG clinical trial consortium, a collaboration of gynaecology and obstetric departments in the Netherlands.

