### Randomisation

Participating hospitals will be randomised to either concealed or revealed CPR results for the duration of the study. Hospitals will be randomised using a computer-generated algorithm, stratified by country and number of deliveries per year.

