### Sample size calculation

We estimate a reduction of the incidence of the composite adverse neonatal outcome from 12 to 8%. The background risk of 12% is extrapolated from the existing literature on RFM as applicable to our population [2, 21, 25–29]. This is an extrapolation because there has been heterogeneity in reported outcome measures in RFM studies. We anticipate an incidence of stillbirth and neonatal mortality (< 28 days) of 0.5%, and an incidence of Apgar score < 7 at 5 min and/or pH < 7.10 umbilical artery and/or emergency delivery for fetal distress of 11% (indicative for peripartum asphyxia). The less common events are grouped into severe neonatal morbidity and include: need for cooling, respiratory distress syndrome, hypoxic ischemic encephalopathy, sepsis, necrotizing enterocolitis and, supplementary oxygen therapy (> 4 days). For severe neonatal morbidity we anticipate an incidence of 1% of which 0.5% overlaps with peripartum asphyxia.

Based on these assumptions, a total of 2160 patients obtained from 24 clusters with 90 patients per cluster (equal numbers of control and intervention), achieve 80.06% power to detect a difference in the primary outcome from 12 to 8%, with an alpha of 5%, and an intra-cluster correlation of 0.002.

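### The primary model specifies random slopes per hospital, but each hospital stays in one arm, so a slope on arm has a variance and covariance that the data cannot identify

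*Protocol article*

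**What the plan says.** The protocol article describes a "cluster randomised controlled clinical trial with randomisation at hospital level" (Study design). Under Randomisation it adds: "Participating hospitals will be randomised to either concealed or revealed CPR results for the duration of the study". No crossover or staged switch is described, so every woman in a given hospital is managed under the same condition.

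The Data analysis plan then specifies the primary relative risk "using a generalized linear mixed model with log link and binomial distribution, with random intercepts and random slopes per cluster". It does not say which variable carries the slope. For continuous secondary outcomes the slopes are left to judgement; the primary model has no such qualifier. The model is carried further: "Dichotomous secondary outcomes will be analysed using the same method as the primary outcome".

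The Sample size calculation plans "a total of 2160 patients obtained from 24 clusters with 90 patients per cluster (equal numbers of control and intervention"). Its stated power is 80.06% for risks of 12% and 8%, computed "with an alpha of 5%, and an intra-cluster correlation of 0.002".

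**The concern.** A random treatment slope lets the treatment effect vary between hospitals. Estimating that variation needs both conditions within the same hospital, as in a crossover or stepped-wedge design. Here no hospital provides both, so the primary-analysis sentence asks for something the design cannot supply.

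This is a statement in the text, not a detail left to a later plan. At stake is whether the primary model can be run as written. A singular-fit warning or an arbitrary variance decomposition would invite a change of model at the analysis stage, and any reported spread of treatment effects across hospitals would have no basis in the data.

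**Working it through.** **Inputs.** 24 hospitals of 90 women, equal arms, so 12 hospitals and 1080 women per arm; risks 12% and 8%; intra-cluster correlation (ICC) 0.002; alpha 5%, taken as two-sided because sidedness is not stated (all from Sample size calculation). Arm is constant within hospital (Randomisation).

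**1. The plan's own figure.**
- Design effect: 1 + (90 − 1) × 0.002 = 1.178. Effective size per arm: 1080 / 1.178 = 916.8.
- Standard error of the difference: √[(0.12 × 0.88 + 0.08 × 0.92) × 1.178 / 1080] = 0.01398. Ratio: 0.04 / 0.01398 = 2.861.
- Two-sided normal power: 81.6% (81.5% with a pooled null variance), against the stated 80.06%. The figure is reproduced to within two points, so the inputs are understood as intended.

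**2. Counting parameters.** Write the log risk in hospital j as b0 + b1·arm + u0j + u1j·arm, with Var(u0) = s0², Var(u1) = s1², Cov(u0, u1) = s01. Because arm is constant within hospital, each hospital contributes either u0j or u0j + u1j:
- concealed hospitals: between-hospital variance v0 = s0²;
- open hospitals: between-hospital variance v1 = s0² + 2·s01 + s1².

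That gives two estimable quantities for three parameters.

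**3. How wide the ambiguity is.** On the log scale, ICC 0.002 at 12% risk corresponds to a variance of about 0.002 × 0.88 / 0.12 = 0.0147; 0.0144 (SD 0.12) is used below. Each of these valid covariance matrices gives v0 = v1 = 0.0144:

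| s0² | s01 | s1² | v1 |
|---|---|---|---|
| 0.0144 | 0 | 0 | 0.0144 |
| 0.0144 | −0.005 | 0.01 | 0.0144 |
| 0.0144 | −0.01 | 0.02 | 0.0144 |
| 0.0144 | −0.0144 | 0.0288 | 0.0144 |

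On one simulated trial of this design all four gave a log-likelihood of −246.7067. The likelihood depends on the three parameters only through v0 and v1, so the equality is exact and more data would not break it. In general, v1 = v0 requires s01 = −s1²/2, and a valid covariance requires s01² ≤ s0²·s1². Hence s1² can lie anywhere from 0 to 4 × 0.0144 = 0.0576, that is, an SD of hospital-specific log relative risks anywhere from 0 to 0.24.

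**4. What happens to the arm effect.** Since the likelihood depends only on v0 and v1, the fixed effect b1 is the same anywhere on the flat ridge. Fitting the identifiable version (a separate variance per arm) to 400 simulated trials per scenario, at ICC 0.002 to 0.01, the optimiser converged every time. The median standard error was 1.004 to 1.015 times that of the random-intercept model. At ICC 0.002 the median shift in log relative risk was about 0.01, with single trials up to about 0.1. Wald power at 12% against 8% was about 80%, against 82% for the random-intercept model. These fits used the two-variance form, so they do not show how a package handles the redundant three-parameter form.

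**5. Small-sample reference, for context.** A cluster-level approximation using a maximum-likelihood variance and a normal reference gives a type I error of about 5.4% to 5.6% at ICC 0.002. A comparison of raw hospital proportions referred to the normal distribution gives about 6.3% (2 × P(t22 > 1.96)). With t on 22 df (critical value 2.074), approximate power is 78.1%.

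**The case against.** **The treatment effect survives.** A reader might infer that the primary relative risk, interval and p-value could not be obtained and would have to come from an improvised model. The documents do not support that. The redundant parameters are nuisance parameters, and the stated model is equivalent to one with arm-specific between-hospital variances, which is fittable and changes the result little on average. This objection stands and limits the point to the specification.

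**The slope variable is inferred.** A slope on calendar time or a patient characteristic would be estimable. This stands as a condition. But the plan names no such variable, and arm is the only effect the model is said to estimate, so the sentence needs changing on either reading.

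**Forcing intercept and slope to be independent makes the model fittable.** True, but then s1² = v1 − v0, which can represent only extra variance in the open arm and not a hospital-specific effect. No such constraint is stated.

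**Convergence.** A reader might infer that a log-binomial model will fail here. Trouble arises when fitted risks approach 1; the planned risks are 8% to 12%, and rarer outcomes lie further away. Nor is a zero variance estimate a failure. At ICC 0.002 it would occur for a lone random intercept in about 34% of trials (P(F(22, 2136) < 1/1.178) = 0.335), and the model then becomes an ordinary log-binomial regression. The recommended model would share this behaviour.

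**Small-sample correction.** A reader might infer that the plan commits to uncorrected Wald inference. It does not say so, and a degrees-of-freedom method or a fallback model may sit in a full protocol or statistical analysis plan that is not shown. This is not a finding.

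**Conclusion.** The point holds as a fault in the stated primary model. If the slope is on arm, its variance and its covariance with the intercept are not identified under a parallel cluster design: three parameters for two estimable variances. At the planned ICC, slope variances from 0 to 0.0576 are indistinguishable when the arms have equal between-hospital variance. The model is over-parameterised, likely to produce a singular fit, and cannot yield hospital-specific treatment effects. The same applies to the dichotomous secondary outcomes.

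The direct effect on the estimated relative risk is small on average. The reason to correct the sentence is that the primary analysis should be runnable and interpretable as written. The conclusion rests on reading arm as the slope variable and on an unconstrained covariance; the log-scale figures assume normal hospital effects with variance near 0.0144.

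**What to change.** In the Data analysis plan, replace the random-effects wording with a random intercept per hospital and a fixed effect of arm, for the primary outcome and for the dichotomous secondary outcomes. If a slope on another variable was meant, name that variable and say why it is needed. This is a change to one sentence and needs no new data or change in conduct. Its statistical cost is the assumption of equal between-hospital variance in both arms; if that is unwelcome, arm-specific variances can be specified directly.

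Optionally, the same sentence could state a small-sample reference for 24 clusters, for example t with about 22 df (fewer if stratification factors are adjusted for) and a REML-type variance. That choice has a price. Approximate power becomes about 78%, against the stated 80.06% and the 81.6% from the normal approximation above. With 90 women per hospital, 13 hospitals per arm (26 × 90 = 2340 women) would give about 81.5%. The inflation it guards against is small at the planned ICC.

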### Economic evaluation

A cost-effectiveness analysis (CEA) will be performed based on the empirical data we will obtain in the trial. The CEA will be performed from both a healthcare- and societal perspective. The primary outcome in the short-term CEA will be the composite neonatal outcome. Costs will include pregnancy monitoring, delivery according to place of birth (hospital or at home), mode of delivery and postnatal care. Additional analyses will be performed to determine the effect of maternal biomarker-based risk selection (normal or abnormal PlGF) on cost-effectiveness.

The long-term economic impact and CEA will be evaluated in a scenario analysis comparing costs of CPR monitoring to costs of current routine monitoring, including long-term costs caused by poor neonatal outcome such as physical and intellectual disability. The cost difference will be related to the difference in life-years for the newborns to reflect the effect of avoided stillbirth.

The budget impact analysis of management based on CPR in women with RFM will be performed according to the ISPOR guidelines from a societal perspective as well from the health insurance and/or Dutch healthcare budgeting framework perspective [32]. Also the incremental cost effectiveness ratio will be calculated by dividing the difference in costs between expectant management and the intervention by the difference in quality-adjusted life years between usual care and intervention.

## Ethics and disemmination

### Patient consent

Eligible patients obtain verbal and written information when the CTG appears normal. The information can be read during the CTG recording and a short animation video that has been developed to provide a study summary in laymen’s terms can be watched. If a patient agrees to participate, written informed consent will be obtained by an authorized person. Additional consent will be obtained to store the residual material of the maternal blood sample in a biobank for 50 years and to be approached for follow-up- and future research.

### Data collection and confidentiality

Data will be collected via Castor Electronic Data Capture, a web-based electronic case record form that meets Good Clinical Practice (GCP) guidelines. All data will be handled confidentially and access to the key of the security code is strictly limited. After termination of the study the research data will be preserved for 15 years in keeping with the General Data Protection Regulation.

Participants may withdraw at any time for any reason if they wish to do so. Unless they refuse to allow further data collection, trial data will be collected for the intention-to-treat analysis. If a participant refuses the study intervention for any reason, follow-up (questionnaires) will be continued.

Data management procedures and data collection forms can be found on the website [30].

### Monitoring and safety

An independent data monitoring committee will monitor data capture in compliance with GCP and other (inter) national rules and regulations in order to achieve high quality research and secure patient safety. Each participating center will have a monitor visit at the start- and end of the study and during the recruitment period. Serious adverse events and any other significant problems will be reported to the ethics committee of the University Medical Center of Groningen. An independent Data Safety Monitoring Board (DSMB) has been established. The DSMB will review outcome data of the first 600 and 1200 patients. An interim analysis for efficacy will not be performed. The DSMB can recommend early termination of the study in case of serious safety concerns and a perceived negative benefit-risk balance. These agreements have been documented in a DSMB charter which can be found on the website [30].

### Ethics

The trial will be conducted in compliance with the contemporary version of the Declaration of Helsinki, the ICH GCP and other applicable regulations. Ethical approval was obtained from the ethical board of the University Medical Center of Groningen, the Netherlands (METc 2019.488) and from Mater Misericordiae Ltd. Human Research Ethics Committee, Australia (HREC/MML/65382). The ethics approval from the UK is pending, with recruitment planned to begin once approval has been granted.

### Dissemination plan

Dispersion of the trial results will be accomplished by publication in an international peer-reviewed scientific journal and by presentations at (inter) national conferences. When the results of the trial warrant changes in the standard treatment guidelines of RFM, we anticipate that the widespread execution of the trial in sites throughout the Netherlands, the UK and Australia will aid in its implementation.

## Discusson

The lack of diagnostic tools to correctly identify the fetuses at risk for adverse outcomes and imminent stillbirth as a result of placental insufficiency within the large group of pregnancies reporting RFM, is an everyday problem for midwives and obstetricians. The CPR is a promising functional marker to detect placental insufficiency and is increasingly implemented in clinical practice. Large practice variation in the use of Doppler measurements for the indication of RFM exists among both maternity hospitals and healthcare professionals. The utility of the CPR on which to base clinical management and time delivery in women with perceived RFM has not been investigated. It is possible that expedited delivery does not reduce the adverse neonatal outcomes. Furthermore, other functional markers (including serum biomarkers and the component pulsatility indices of the umbilical artery, middle cerebral artery and uterine artery) have not been assessed for RFM and risk calculation. Evidence based guidelines on the use of Doppler assessment for the indication of RFM are needed.

### Strengths and challenges

A strength of this proposed study is the large control group. The concealed arm (control group) is, however, a logistic challenge. Several options to conceal the CPR result have been explored. Concealing the CPR result at software- or ultrasound device level appeared to have many organisational (many systems available for both ultrasound machines and ultrasound data capture software) and legal limitations. Despite considerable efforts by ultrasound companies and ultrasound data capture software builders, this blinding method proved to be unfeasible. The current approach in which the CPR is concealed for the treating physician was considered to be a proper alternative and is extensively described in the methods section.

Another strength is the sampling of serum biomarkers. The predictive value of maternal biomarkers to detect placental insufficiency at term is currently unknown. In combination with the obtained Doppler results we hope to facilitate the first steps in developing an individualised prediction model to detect pregnancies at risk for placental insufficiency.

The cluster design was preferred over randomisation at the individual patient level because it was expected that both clinicians and the pregnant women would not be willing to wait for spontaneous delivery once an abnormal CPR is measured. Randomisation at cluster level was postulated to lead to a better implementation of the intervention in participating sites.

This cluster RCT will determine whether the CPR is an effective marker to guide management in pregnancies at term complicated with RFM. If the CPR proves to be an adequate indicator for delivery, expedited delivery will be restricted to the smaller number of compromised fetuses suffering from placental insufficiency, reducing their stillbirth risk and improving long-term health. Moreover, a larger group of women with perceived RFM can be reassured and monitored less intensively, reducing their burden of unnecessary intensified monitoring and interventions, resulting in substantial lowering of health costs.

## Data Availability

The datasets used and/or analysed during the current study will be available from the corresponding author on reasonable request.

## Abbreviations

ASQ: Ages and Stages Questionnaire
CBCL: Child Behaviour Checklist
CEA: Cost-effectiveness Analysis
CPR: Cerebroplacental Ratio
DSMB: Data Safety Monitoring Board
EQ-5D-5L: European Quality of life 5-Dimension 5-Level
GCP: Good Clinical Practice
ISPOR: International Society for Pharmacoeconomics and Outcomes Research
METc: Medical research ethics committee
NTR: Dutch trial registry
PCL-5: Posttraumatic stress disorder Checklist for DSM-5
PlGF: Placental Growth Factor
RFM: Reduced fetal movements
RR: Relative Risk
SPIRIT: Standard Protocol Items Recommendations for Interventional Trials
sFlt-1: Soluble fms-like tyrosine kinase-1
UK: United Kingdom
WDEQ: Wijma Delivery Expectancy/Experience Questionnaire
